### Randomization and allocation sequence

The Research Electronic Data Capture® (REDCap®) software will be used for randomization. After agreeing to participate in the study, patients will sign an informed consent form. The research team will add in REDCap® the following information: sociodemographic data (age, schooling level, profession, religion, etc.) and clinical data (disease profile, New York Heart Association [NYHA] classification, previous hospitalizations in the last 12 months, other diseases, HF etiology, application of the Borg, SAK 2, and Barthel scales). After all variables are included, the electronic platform randomizes the patient. The allocation sequence is a randomization based on a single 1:1 sequence.

### Blinding

Patient randomization will be conducted by a researcher not involved in data collection. Physical therapists will be blinded for the collection of the outcomes (perceived dyspnea and patient experience) and data analysis. Data will be collected by researchers uninvolved in the intervention but who are not blinded to group allocation due to the nature of the protocol and the outcomes. Data analysis will be performed by a statistician independent from the study.

### Study variables

Dyspnea: dyspnea will be assessed by the modified illustrated Borg scale [14]. One of the researchers responsible for collecting data will ask patients to assess the degree of perceived dyspnea at rest and immediately after the intervention in all interventions according to a list of figures that reflect a numerical order from 0 to 10. In it, 0 corresponds to no dyspnea, 0.5–2 corresponds to minor dyspnea, 3–4 corresponds to mild dyspnea, and 5–10 corresponds to severe dyspnea [22].Patient experience: patient experience will be assessed by the NPS tool and the Likert scale. The NPS is intended to measure the satisfaction level of customers or patients regarding a product or service. The scores are assigned on a numerical scale from 0 to 10 and are divided into three categories: detractors (0 to 6), passives (7 or 8), and promoters (9 or 10) [15]. The Likert scale consists of psychometric responses commonly used in opinion surveys when responding to a questionnaire. Respondents specify their level of agreement with a statement or question as follows: strongly disagree, disagree, neutral, agree, and strongly agree. An open-ended interview will also be conducted at the end of the intervention by a researcher who is not involved in the application of the early mobilization protocol to preserve the subjectivity associated with patient experience.Risk of falls: participants must meet the eligibility criteria before being enrolled in the study. The risk of falls will be assessed with the SAK 2 scale. The scale assesses the following variables: disorientation/confusion, frequent urination, difficulty walking, lack of caregiver, postoperative period, number of medications administered before the fall (up to 72 h), and previous falls. The score ranges from 0.5 to 17 points, divided into low (≤ 6.0), moderate (6.5–10), or high (≥ 10.5) risk of falls. This scale is systematically used at HCPA and is part of the daily assessment conducted by the nursing team; the results are recorded in the patients’ medical records [16].Sociodemographic data: if the participant meets the eligibility criteria and agrees to participate in the study, sociodemographic data will be collected before randomization using a questionnaire including questions about age, gender, education, occupation, current and previous hospitalizations, disease and associated comorbidities, and use of medications.Functional independence: functional independence will be assessed before randomization by the Barthel scale, which considers the degree of help needed for feeding, bathing, activities of daily living, dressing, bowel control, bladder control, toilet use, transfers, mobility, and stairs. The score ranges from 0 to 100, and the higher the score, the greater the functional independence and the less the need for help to perform activities of daily living [17].

### Data collection

The primary outcome should be assessed immediately before and after each mobilization therapy session, less than 5 min before the start and immediately after the completion of the mobilization protocol.

At the end of the interventions, patient experience will be assessed in both groups. Patients included in the study will be contacted in the ICU within 48 h of the end of the intervention and will be invited to answer questions related to their experience during the mobilization protocol with and without the use of immersive VR.

The outcomes will be collected by two researchers previously trained in the pilot study. The researchers involved in data collection are not involved in applying the study protocol and are not blinded to group allocation due to the nature of the protocol and the outcomes assessed, such as patient experience.

### Data management

In both groups, patients will be treated according to the hospital’s protocol of good safety practices. Any solicited and spontaneously reported adverse events (such as loss of venous access or probes, falls, nausea or dizziness, or symptomatology of hemodynamic instability) will be recorded for further reporting.

Data will be stored in the REDCap® platform. Only researchers trained on this software and in the pilot study will collect data. Data will only be extracted from the REDCap® platform after the inclusion and establishment of the total number of participants. Data of excluded patients will be stored in an exclusion control list for future data reporting.

### Statistical analysis

The database will be built on the REDCap® platform. All data will be analyzed on Statistical Package for the Social Science (SPSS) version 22.0 for Windows®. The Shapiro–Wilk test will be used to assess data normality. For quantitative data, categorical variables will be expressed as absolute and relative frequencies, and continuous variables will be expressed as means and standard deviations or medians and interquartile ranges.

To address the statistical analysis of multiple time point measurements for the primary outcome intragroup and intergroup, repeated measures tests will be done using Generalized Estimating Equations (GEE). Also, associations between vital signs and perception of dyspnea will be analyzed by the GEE test too.

Chi-square will be used for association of categorical variables, and analysis of variance (ANOVA) or Kruskal–Wallis to compare the categorized sensation of dyspnea with the other variables. Depending on variable behavior or characteristic, the correlations will be analyzed by the Pearson or Spearman coefficient. The significance level will be set at 5% (*p* < 0.05). All analyses will be performed by intention to treat.

Information obtained from the Likert scale and the NPS tool will be analyzed using resources from the NVivo software version 12 for Windows®, which combines the main tools required for working with texts, mixed methods, and data from the literature.

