### Outcomes

The primary outcome is the assessment of perceived dyspnea in all sessions in both groups using the modified Borg scale [14].

The secondary outcome is the assessment of patient experience at the end of the early mobilization protocol with and without immersive VR using the Net Promoter Score (NPS) tool and the Likert scale [15] as well as an open-ended interview.

Other variables include (a) assessment of vital signs, (b) collection of sociodemographic data, (c) assessment of risk of falls, and (d) assessment of functional independence. To assess the risk of falls, the standard Severo-Almeida-Kuchenbecker (SAK) 2 scale [16] will be used. To assess functional independence prior to hospitalization, the Barthel scale [17] will be used. Both scales are validated.

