### Sample size

The study by Nomura et al. [19] used the Borg scale in the first 24 h to assess the effects of medication on the sensation of dyspnea and other outcomes. In the first 24 h, the patient’s sensation of dyspnea significantly improved, with a significant reduction in the Borg scale score [19].

Initially, applying the Borg scale obtained an index of 7. After intervention, the index ranged from 2 to 3. This study showed that after the first 24 h the patient tends to have less changes in the dyspnea sensation, given the use of medication [19]. Based on the literature, we believe that 1 point is a considerable change score, since the patient would probably not have a more significant change due to the compensation of the clinical condition.

The sample size was estimated to detect differences in mean dyspnea between the intervention and control groups using the Borg scale, with a difference of 1 point being relevant for the study. For this purpose, the online version of the power and sample size (PSS) Health tool was used [20]. Considering an 80% power, a 5% significance level, and a 1.6-point standard deviation [19, 21], a total sample size of 54 participants was calculated, with 27 participants in each group. To account for 20% of possible losses and refusals, the total sample size will need to include 66 participants (33 in each group). Seeking to reach the appropriate sample number to conclude the study, a daily screening will be carried out by the research team of patients meeting the inclusion criteria admitted to the study site.

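### Comparing categorised dyspnea with the other variables by ANOVA or Kruskal–Wallis suits repeated 0–10 scores poorly; the GEE already planned would serve better

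*Protocol article*

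**What the plan says.** Under Outcomes, the protocol article states: "The primary outcome is the assessment of perceived dyspnea in all sessions in both groups". Data collection places a reading just before and just after every session. Intervention and groups allows at most three sessions, so a patient contributes up to 3 × 2 = 6 scores. Study variables describes the 0–10 scale in four bands: 0, 0.5–2, 3–4 and 5–10.

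The Statistical analysis section uses three approaches that matter here:

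- GEE for the repeated primary outcome, within and between groups. It adds that "associations between vital signs and perception of dyspnea will be analyzed by the GEE test too".
- ANOVA or Kruskal–Wallis "to compare the categorized sensation of dyspnea with the other variables".
- A general sentence that "the correlations will be analyzed by the Pearson or Spearman coefficient", without naming the variables.

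The section does not say which dyspnea reading is categorised, which cut-points apply, or what the other variables are. All tests use the 5% level.

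**The concern.** ANOVA and Kruskal–Wallis treat every record as independent. Dyspnea here is a repeated measure, and the plan recognises this by choosing GEE for the main comparison and for vital signs. For the remaining variables it moves to a coarsened score and a one-record-per-patient test.

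The clause can be followed in two ways. Pooling the readings makes p-values too small and produces spurious correlates of dyspnea. Taking one reading per patient is valid, but it coarsens the score, treats ordered bands as unordered groups and leaves up to five readings unused, so real correlates are missed more often. What is at stake is the reliability of secondary statements about which patient characteristics go with breathlessness during mobilisation.

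**Working it through.** **Inputs from the protocol article.** SD 1.6 and 54 patients, or 66 with losses (Sample size); up to six readings (Intervention and groups, Data collection); four bands (Study variables); 5% level (Statistical analysis).

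**Assumed, because the article gives no figure.** Within-patient correlation (ICC) 0.3, 0.5 or 0.7; mean Borg score 2 to 2.5 in the power and error simulations; the Study variables bands as cut-points; equal correlation between all readings. The simulations do not impose the exclusion of resting scores of 4 or more.

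**The plan's own figure.** There is none for these analyses. The article's 54 and 66 serve here only as numbers of patients. The sample-size inputs give 2 × (1.96 + 0.842)² × 1.6² / 1² = 40.2, so 41 per arm (two-sided) rather than 27. That is a separate matter, and nothing below rests on it.

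**Way 1: all six readings pooled.** For a variable that is constant within a patient, the design effect is 1 + (6 − 1) × ICC. A nominal 5% test then has a true error of about 2 × [1 − Φ(1.96 / √design effect)].

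| ICC | Design effect | Approximate error | Simulated Spearman | Simulated ANOVA | Simulated Kruskal–Wallis |
|---|---|---|---|---|---|
| 0.3 | 2.5 | 0.22 | 0.21 | 0.17 | 0.17 |
| 0.5 | 3.5 | 0.29 | 0.28 | 0.27 | 0.26 |
| 0.7 | 4.5 | 0.36 | 0.35 | 0.41 | 0.42 |

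The simulation used 54 patients, mean 2.5, the four bands and 4,000 runs per row. The formula agrees with the Spearman column. The two planned tests run at about 17–42%. With three readings pooled (54–66 patients, mean 2) they run at about 9–22%.

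**Way 2: one banded reading per patient.** Simulated type I error is about 0.04–0.05, so the test is valid. The loss is in power and has two sources.

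- *Banding.* At a true correlation of 0.3 with 66 patients (mean 2, 6,000 runs), power is about 42–46% on the bands and 63% for Spearman on the same reading uncategorised. With 54 patients it is 33–37% against 55%. The bands keep about 83–88% of the variance of one reading. Much of the extra loss comes from testing ordered bands as unordered groups, which spends up to three degrees of freedom.
- *Dropped readings.* One reading carries (1 + 5 × ICC) / 6 of the information in the mean of six: 2.5/6 = 0.42, 3.5/6 = 0.58 and 4.5/6 = 0.75. Multiplied by about 0.88 for banding, 0.37, 0.51 and 0.66 remain.

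Power with 54 patients and a correlation of 0.45 between the variable and the patient's underlying dyspnea:

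| ICC | One banded reading, ANOVA | One full-scale reading, Spearman | Mean of six readings |
|---|---|---|---|
| 0.3 | 0.25 | 0.39 | 0.82 |
| 0.5 | 0.42 | 0.60 | 0.89 |
| 0.7 | 0.58 | 0.77 | 0.92 |

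The mean of six stands in for a repeated-measures model. GEE itself was not simulated, and the stand-in presumes that the association is the same at every reading.

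**The case against.** The strongest reply is that the plan sends repeated readings to GEE by design, so nothing suggests they would be pooled elsewhere. Which reading is categorised, and against what, is detail that a condensed article may leave to a fuller document. The analyses are supportive.

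Much of this stands. Pooling is only one way to follow the clause, and its error rates depend on an assumed correlation. The missing detail is not itself the fault. But the choice of ANOVA or Kruskal–Wallis on a categorised score is stated. Even in its valid form it is weaker than a method the plan already uses.

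A reader might go further on four points, and the article does not support them:

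- *That dyspnea associations in general are tested by simple correlation.* The Pearson/Spearman sentence does not mention dyspnea and may concern other pairs, such as Barthel and SAK 2.
- *That one question gets two tests.* Vital signs are assigned to GEE first, so the other variables most naturally means the rest.
- *That most of the information is lost.* The bands keep most of a single reading. Less than half remains only if readings are also dropped and the ICC is below about 0.5, a value the article does not give.
- *That grouping by dyspnea is always the wrong way round.* Patient experience is collected after the intervention, so for that variable dyspnea comes first in time.

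**Conclusion.** The concern holds for the ANOVA/Kruskal–Wallis clause, applied to variables other than vital signs. Pooling six readings would raise the false-positive rate to about 17–42%. One banded reading keeps the 5% level but cuts power to about 42–46%, against 63% for the uncategorised score (true correlation 0.3, 66 patients), with the remaining readings unused. The sizes rest on an assumed ICC of 0.3–0.7, assumed Borg means, and the Study variables bands as cut-points. The direction does not depend on the exact values within those ranges.

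The clause should be changed, but the consequence is limited: neither the randomised comparison by GEE nor the sample size is affected.

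**What to change.** Replace only the ANOVA/Kruskal–Wallis clause, for example with: *Associations of dyspnea with baseline variables (sociodemographic and clinical data, SAK 2, Barthel) will be estimated by GEE, with the 0–10 Borg score as outcome, the variable as covariate, and session, time (before or after the session) and group as terms. The Borg bands will be used for description only.*

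Keep the Pearson/Spearman sentence, limited to variables with one value per patient. Patient experience should not be a covariate for dyspnea recorded before it. Relate it instead to a single uncategorised dyspnea summary per patient, named in advance, such as the mean of the post-session scores.

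The cost is a change of wording, with the same data and software. The downside is that results are slopes per unit of the variable rather than a band-by-band table; a descriptive table by band can still be shown.

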Filling this gap could improve the rational and direct incorporation of new technologies in health care, allowing for better outcomes in this clinically vulnerable population. This randomized clinical trial hypothesis is that patients hospitalized due to ADHF undergoing an early mobilization protocol with immersive VR will have improved perceived dyspnea as well as a positive patient experience with the technology compared with those undergoing a conventional mobilization protocol without immersive VR.

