Cardiovascular rehabilitation in the hospital phase aims to optimize both physical and psychological outcomes for the patient. The goal at this juncture is not necessarily intensive rehabilitation, but to initiate a process that ensures patient safety and comfort while also laying the groundwork for post-discharge activities. At this stage, mild-intensity exercises are deemed optimal [18], and the proposed timings sufficiently meet this intensity. Monitoring of vital signs and of the patient’s perception of exertion is essential to maintaining this balance.

All interventions will be performed with or without the use of immersive VR headsets, videos, and earbuds, as previously described. To assess patient opinion at the end of interventions, the NPS tool and the Likert scale [15] will be used. In addition, an open-ended interview will be conducted to further explore quantitative results related to patient experience regarding the proposed interventions in both groups.

Regarding adherence to the study protocol, the research team highlights that mobilization therapy is recommended in the usual treatment of hospitalized patients with ADHF. The proposed exercise protocol does not differ from the mobilization therapy currently offered by the hospital care team; the only difference is the impact evaluation of using VR during mobilization. If patients accept to participate, the research team will explain to both groups that the study requires some additional tests before starting the mobilization protocol, immediately after, and up to 2 days at the end of the protocol. The research team is responsible for reinforcing the importance of the mobilization protocol and the test to participate in the study.

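### The numeric patient-experience outcome (NPS and Likert) is assigned to NVivo, in conflict with the plan's own SPSS statement, and no between-group test is named for it

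*Protocol article*

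**What the plan says.** All references are to the protocol article.

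- **Hypothesis (Introduction).** Patients mobilized with VR are expected to have improved dyspnea "as well as a positive patient experience with the technology compared with those undergoing a conventional mobilization protocol without immersive VR".
- **Outcome (Outcomes).** "The secondary outcome is the assessment of patient experience at the end of the early mobilization protocol with and without immersive VR", measured by the NPS, the Likert scale and an open-ended interview. Data collection says that experience is assessed in both groups.
- **Scales (Study variables).** For the NPS, "The scores are assigned on a numerical scale from 0 to 10 and are divided into three categories": detractors 0–6, passives 7–8, promoters 9–10. The Likert responses are "strongly disagree, disagree, neutral, agree, and strongly agree".
- **Nature of the data (Participant timeline and study protocol).** "an open-ended interview will be conducted to further explore quantitative results related to patient experience". The article thus treats the NPS and Likert results as quantitative and the interview as the qualitative complement.
- **Analysis (Statistical analysis).** "Information obtained from the Likert scale and the NPS tool will be analyzed using resources from the NVivo software version 12 for Windows", a program described as one "which combines the main tools required for working with texts, mixed methods, and data from the literature". The opening of the same section places all data in SPSS version 22.

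**The concern.** The only analysis sentence that names the NPS or the Likert scale sends them to software that the article describes in terms of texts, mixed methods and literature data. The interview, which would suit such software, is not mentioned in the analysis section at all. The two assignments look transposed.

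The NVivo sentence also cannot be squared with the statement that all data are analyzed in SPSS. Two analysts could follow this section in good faith and treat the single secondary outcome differently: one would code and describe it, the other would tabulate it by arm.

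This matters because the hypothesis for this outcome is comparative. Patient experience is also subjective, and both participants and outcome collectors know the allocation (Data collection, Potential biases). For such an outcome, the method of comparison should not be left open until the data are in hand.

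**Working it through.** **Step 1. Match each named method to the outcome it is tied to (Statistical analysis).**

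| Method | Tied to | Patient experience by arm? |
|---|---|---|
| GEE | primary outcome within and between groups; vital signs against dyspnea | no |
| ANOVA or Kruskal-Wallis | categorized dyspnea against other variables | no |
| Pearson or Spearman | correlations, variables not named | no |
| Chi-square | association of categorical variables in general | possible, but neither arm nor outcome is named |
| NVivo | NPS and Likert, by name | no test or estimate stated |
| None | open-ended interview | not applicable |

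Chi-square is therefore the only named test that could reach this outcome, and only by reading a generic line against a specific one.

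**Step 2. What the chi-square route would give up.** Pearson chi-square treats classes as unordered. Applied to the NPS, it also reduces 11 possible scores to three classes. The article gives no NPS distribution or expected effect, so everything below is assumed and serves only to illustrate. The 27 per arm is the article's number before losses.

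Take a proportional odds ratio of 3 in favor of VR.

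- Control 50/30/20% (promoters/passives/detractors). Promoter odds 0.50/0.50 = 1 become 3, so 75%. Detractor odds 0.20/0.80 = 0.25 become 0.0833, so 7.7%. Passives are the remainder, 17.3%.
- Control 70/20/10%. Promoter odds 0.70/0.30 = 2.333 become 7, so 87.5%. Detractor odds 0.10/0.90 = 0.111 become 0.037, so 3.6%. Passives 8.9%.

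Large-sample check of the chi-square power, with noncentrality λ = n Σ (p₁ − p₂)²/(p₁ + p₂) on 2 degrees of freedom:

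- 50/30/20: λ = 27 × (0.0500 + 0.0340 + 0.0547) = 3.75, power 39%.
- 70/20/10: λ = 27 × (0.0194 + 0.0424 + 0.0304) = 2.49, power 27%. Expected counts are small here, and simulation gives somewhat less.

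Simulated power at two-sided 5%, 27 per arm, odds ratio 3. The ranges reflect different assumed splits of scores within the three classes:

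| Control distribution | Chi-square, 3 classes | Mann-Whitney, 0–10 score |
|---|---|---|
| 50/30/20% | 39–40% | 53–59% |
| 70/20/10% | 23–25% | 42–58% |

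The rank test is ahead in both scenarios, but the size of the gain depends on the assumed distribution. These figures compare two tests. They do not measure the effect of the NVivo sentence, for which no arithmetic applies.

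**The case against.** The strongest reply is that a comparison is already available. All data go to SPSS, chi-square covers categorical variables, the significance level is 5%, and all analyses are by intention to treat. The NPS has three defined classes and the Likert scale five, both collected in both arms. On that reading, the NVivo sentence is a clumsy description of a mixed-methods step. The article does list mixed methods among NVivo's uses and does intend the interview to explain the numeric results.

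Much of this stands. A reader might infer that the plan contains no between-group test at all and that half of the hypothesis cannot be answered. The text does not support that: the generic lines can be stretched to NPS classes or Likert levels by arm. What can be said is that no test is named for this outcome, and that the one sentence naming it points elsewhere.

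A second reply is that the test and effect measure for a secondary outcome may sit in an analysis plan that is not shown. That is fair for silence, and the mere absence of a confidence interval or model is not the point here. An explicit assignment that conflicts with another sentence of the same section is different, because it is wording that needs correcting where it stands.

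Third, the three NPS classes are the article's own definition, so using them is not an error by staff. This also stands. The objection to chi-square is only that it discards order and resolution.

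**Conclusion.** The concern holds as a misassignment and an internal conflict. Quantitative secondary-outcome data are sent to NVivo, the same section sends all data to SPSS, the interview has no assigned analysis, and no between-group test is named for an outcome with a comparative hypothesis. This part rests on the text alone.

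The loss of power under the chi-square fallback rests on an assumed NPS distribution and an assumed odds ratio. Only its direction should be relied on. It would be wrong to conclude that the trial cannot address patient experience: the data are planned in both arms, and a suitable comparison needs only to be written down. Randomization, data collection and the GEE analysis of dyspnea are unaffected. Severity: should fix.

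**What to change.** Replace the NVivo sentence in Statistical analysis with wording to this effect:

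- The NPS 0–10 score is the main measure of patient experience. It will be compared between the randomized groups in SPSS by a two-sided Mann-Whitney test at 5%, with an effect estimate and 95% confidence interval. A suitable estimate is the probability that a VR patient scores higher than a control patient, ties counted as half.
- Likert items will be compared in the same way as supportive results, with no claim of multiplicity control, since the article does not say how many items there are.
- Percentages of promoters, passives and detractors will be reported per arm.
- NVivo will be used for the interview text and for integrating it with the quantitative results.

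The statement that all data are analyzed in SPSS should then be limited to the quantitative data.

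The cost is a few sentences and notification to the ethics committee, which Trial status already foresees for protocol changes. No new data or software is needed. Data management says that data are extracted only once the total number of participants is established, so the wording would remain prespecified if settled before that extraction. The article does not show whether it has already taken place.
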